### Statistical Power

For the Outaouais region (n=397,007), the statistical power to detect a 20% decrease from the 2016 to 2019 averages at α=.05 would be 33.1% for suicide mortality, 85.7% for hospitalizations, and 80.4% for ER visits [48]. We do not yet have access to suicidal behavior data specifically for Brest Métropole; however, we estimated the statistical power based on its 2019 population (n=211,156) and published data about the Finistère department as a whole: the suicide rate was 23.4 per 100,000 in 2015 and the hospitalization rate was 227.8 per 100,000 in 2017 [45]. From this lower population but considerably higher rates of suicidal behaviors, the statistical power to detect a 20% decrease at α=.05 in Brest Métropole would be 26.8% for suicide mortality and 99.7% for hospitalizations. We did not find a reported rate of ER visits for suicide attempts in Finistère for the same period; however, cursory calculations indicate a base rate approximating 130 per 100,000 and a statistical power higher than 90%.

Given the low incidence of suicide in the general population, statistical power is often an issue when conducting pre-post rate comparisons. This has been reported as a justification to aggregate suicide mortality and suicide attempts in OSPI-Europe [12]. However, the statistical power benefits of variables aggregation would be marginal compared to including hospitalizations and ER visit rates as distinct primary outcomes, both of which can be assessed with satisfactory statistical power. Moreover, interrupted time series will provide additional benefits relating to the statistical power of this study in two important ways: (1) including a high number of repeated observations (n=120 months) [49] and (2) assessing the intervention effect on the outcome slope in addition to their level [50]. Considering the very different implications of death rates and indicators influenced by service use, we will analyze each primary outcome separately.

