### Study Objective

Our objective is to assess whether implementing a multimodal suicide prevention program across 2 countries—encompassing a universal strategy (a web portal focused on depression and social isolation), selective strategies (training for primary care physicians on depression and training for mental health professionals on suicide risk assessment and management), and indicated strategies (standardized postcrisis outreach and outpatient monitoring practices)—leads to a reduction in outcomes associated with suicidal behavior, such as suicide mortality, hospitalization due to suicide attempts, and visits to emergency rooms (ERs) for suicide attempts, compared to control sites and over time. We hypothesize that after 2 years of the CQFD-I program’s implementation, there will be a 20% reduction in suicide mortality, hospitalizations due to suicide attempts, and ER visits for suicide attempts compared to control sites. This reduction will be observed when comparing the postimplementation phase (beginning in 2022) to the preimplementation phase (ending in 2020).

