The public health and social services of Outaouais have been under the jurisdiction of a single regional authority since 2015 [38]. This is also the case for most regions included in Tables 1 and 2, except for the following: Capitale-Nationale (n=2 distinct health authorities), Montréal (n=10), Côte-Nord (n=2), Gaspésie-Îles-de-la-Madeleine (n=2), and Montérégie (n=3). In the 2019 to 2020 financial year, 437 general practitioners billed universal health insurance of Quebec for services provided in Outaouais, with two-thirds using primary care–specific codes (Données de facturation RAMQ des médecins omnipraticiens, unpublished data, December 2023). This corresponds to 0.72 primary care physicians per 1000 residents (sixth rank). From 2016 to 2019, age-adjusted suicide rate of Outaouais averaged 15.5 per 100,000 overall (11th rank), 24.9 per 100,000 among male individuals (11th rank), and 6.4 per 100,000 among female individuals (seventh rank) (l’Infocentre de santé publique, unpublished data, November 2023). The average rate of hospitalizations for suicide attempts in Outaouais was 53.4 per 100,000 from 2016 to 2019 (eighth rank), and the average rate of ER visits for suicide attempts was 46.8 per 100,000 (10th rank) [35].

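### The stated power belongs to a one-year, one-sample comparison; the planned controlled segmented regression has far less power for the same 20% drop

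*Protocol article*

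**What the plan says.** The Study Objective section expects that "there will be a 20% reduction in suicide mortality, hospitalizations due to suicide attempts, and ER visits for suicide attempts compared to control sites", comparing the postimplementation with the preimplementation phase.

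The Statistical Power section gives "the statistical power to detect a 20% decrease from the 2016 to 2019 averages at α=.05". For Outaouais this "would be 33.1% for suicide mortality, 85.7% for hospitalizations, and 80.4% for ER visits". For Brest, using rates for the surrounding department, it "would be 26.8% for suicide mortality and 99.7% for hospitalizations", and it exceeds 90% for ER visits at an approximate rate of 130 per 100,000. The section names no test, sidedness, time window or comparator. It says of hospitalizations and ER visits, as distinct primary outcomes, "both of which can be assessed with satisfactory statistical power", and adds that "interrupted time series will provide additional benefits relating to the statistical power of this study" through many repeated observations (120 months) and a slope test.

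The Statistical Methods section fixes the analysis: ordinary least squares on monthly standardized rates, three phases, two arms, with a group-specific baseline slope, level changes and slope changes. The program effects are β8+β9 (level) and β10+β11 (trend).

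**The concern.** Power figures support a plan only if they refer to the test that will be run. The figures here use only the site's population, its baseline rate and α. They contain no control sites, although the hypothesis is framed against controls. They also leave out baseline sampling error, trend terms and the actual 60-, 24- and 24-month phases.

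If the planned contrasts have much lower power, the assurance about the two attempt outcomes is wrong. A non-significant result would then be likely even if the program cut events by 20%, and readers relying on the protocol could take it as evidence that the program does not work.

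**Working it through.** **Step 1. Reproduce the stated figures.** Inputs: population 397,007 for Outaouais, with annual rates of 15.5, 53.4 and 46.8 per 100,000 (Outaouais Region and Control Sites); population 211,156 for Brest, with 23.4, 227.8 and about 130 per 100,000 (Statistical Power).

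Formula: power = Φ[(μ0 − μ1 − 1.96√μ0)/√μ1], with μ0 = population × annual rate and μ1 = 0.8μ0.

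Outaouais suicide: μ0 = 61.54, μ1 = 49.23; (12.31 − 1.96 × 7.844)/7.016 = −0.437; Φ = 33.1%. Outaouais hospitalizations: μ0 = 212.0, μ1 = 169.6; (42.40 − 1.96 × 14.560)/13.023 = 1.064; Φ = 85.6%.

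All five exact figures match to within 0.1 point, and Brest ER gives 93.5%. Other designs do not match. For Outaouais suicide / hospitalizations / ER:
- one-sided: 46.6 / 92.2 / 88.7%
- two-year window: 61.4 / 99.2 / 98.3%
- one year against one year: 21.5 / 58.4 / 52.9%
- four years against one: 28.6 / 77.3 / 71.4%
- five years against two: 48.8 / 95.6 / 92.8%

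**Step 2. Power of the planned regression.** Assumptions: 60, 24 and 24 months as dated; independent Poisson monthly counts; a 20% step drop confined to the last phase; two-sided 5%. The Quebec controls total 8,060,579 (the 14 other regions in Table 1), at the same rate as Outaouais. The French controls are assumed to total 9 million, because the article gives no figure.

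Under the stated dummy coding, β9 is the gap at month 84 (counting from 0) between the postimplementation line and the extrapolated preimplementation line, case minus control. In units of the monthly variance, its two parts are:
- baseline line carried to month 84: 1/60 + (84 − 29.5)²/17,995 = 0.1817, against 1/60 = 0.0167 for a simple baseline mean, about 11 times as much;
- start of the postimplementation line: 1/24 + 11.5²/1,150 = 0.1567, against 1/24 = 0.0417 for a simple mean.

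Outaouais hospitalizations: the monthly rate is 53.4/12 = 4.45 per 100,000 and the monthly variance 4.45/3.97007 = 1.121. The case part is 1.121 × (0.1817 + 0.8 × 0.1567) = 0.344. The control part is (4.45/80.606) × (0.1817 + 0.1567) = 0.019. SE = √0.363 = 0.602; effect = 0.2 × 4.45 = 0.89; ratio 1.477. Power = Φ(1.477 − 1.96) + Φ(−1.477 − 1.96) = 31.5%.

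For β8+β9 the effect is unchanged but the SE rises to 0.940, so the ratio is 0.947 and power is 15.7%.

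| Site, outcome | Stated | β9 | β8+β9 |
|---|---|---|---|
| Outaouais suicide | 33.1% | 12.5% | 8.0% |
| Outaouais hospitalizations | 85.7% | 31.5% | 15.7% |
| Outaouais ER | 80.4% | 28.2% | 14.4% |
| Brest suicide | 26.8% | 11.2% | 7.5% |
| Brest hospitalizations | 99.7% | 61.6% | 30.3% |
| Brest ER | >90% | 39.9% | 19.4% |

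Simulating the full 12-parameter fit 5,000 times per outcome agrees: for hospitalizations, 29.4 / 15.8% in Outaouais and 59.3 / 30.5% in Brest. French controls of 2 to 20 million move Brest hospitalizations (β9) only from 58% to 62%.

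**Step 3. Is the gap an artifact of the scenario?** For Outaouais suicide / hospitalizations / ER:
- 20% drop in both later phases, tested by β8+β9 (which then counts the effect twice): 18.0 / 48.9 / 44.0%. Brest hospitalizations reach 83.9%.
- joint level-and-slope test, step drop: 10.7 / 26.9 / 24.0%.
- trend contrast β10+β11: 5% for a step drop; 7.1 / 12.4 / 11.5% if the drop builds linearly to 20% over the 24 postimplementation months.
- 120 months instead of the 108 that the dates give (60 + 24 + 24): β9 rises only to 14.0 / 36.5 / 32.7%.
- overdispersion of 1.5, or first-order autocorrelation of 0.2 (both assumed): Outaouais hospitalizations fall to about 23% (β9) and 12% (β8+β9).

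**Step 4. Where the loss arises.** Drop the trend terms and compare 60 with 24 months against controls. For Outaouais hospitalizations the case counts are 1,060 and 339.2. The SE of the log ratio of rate ratios is 0.0637 including controls; |ln 0.8| = 0.2231; power = Φ(0.2231/0.0637 − 1.96) = 94%. Depending on scale and on whether control noise is counted, Outaouais has about 47–50 / 94–96 / 91–93%, and Brest about 40–43 / >99 / 98–99%. The differential-trend terms therefore cause the loss.

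**The case against.** The arithmetic in the power section is right for the test it implies, and the section does not call its figures the power of the regression. It speaks of a decrease from past averages, then of pre-post comparisons, and brings in the time series as a further benefit. That is fair, but no other figures are given, and the conclusion of satisfactory power is carried over to a study analyzed only by the regression.

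The longer series does contain more events than the single year behind the figures, so it would be wrong to say that a time series can add nothing. This stands: Step 4 shows a phase-average comparison doing better than the stated figures. The added-power claim fails for the contrasts the protocol names, because the trend terms cost more than the extra months give.

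Power is not the only reason for separate outcomes. The protocol also cites their different meaning and differing data sources, so the separation survives any restated figure. The populations and dates are fixed, no sample size depends on this paragraph, and low power for suicide is already conceded.

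The size of the shortfall depends on the assumed effect path, and on the most favorable path Brest hospitalizations reach about 84%. That path counts the effect twice in the sum and still falls below the stated 99.7%. None of the remaining points restores the stated figures.

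**Conclusion.** The concern holds. The stated power is that of a different and simpler test from the one planned. For a 20% postimplementation step drop, the planned level contrast has 16–32% power for hospitalizations and 14–28% for ER visits in Outaouais, and 30–62% and 19–40% in Brest; the lower value in each range is the contrast as the protocol writes it. Suicide power is 8–13% at both sites. The statements that the attempt outcomes have satisfactory power and that the time series adds to it are unsupported for the planned analysis.

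The exact values rest on the Poisson assumption, the effect path, equal control rates and an assumed French control population. The last two hardly matter. Overdispersion or positive autocorrelation would lower power further.

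**What to change.** 1. Replace the figures with power for the contrasts to be tested, analytic or simulated, on the 60/24/24-month series with controls. State the sidedness, the effect path and a range for overdispersion and autocorrelation.
2. Delete the claim that the time series adds power, and the word satisfactory, unless the restated figures support them. Use 108 months, as the dates give.
3. Optionally, if the sponsor wants power at the advertised level, name the phase-average rate ratio against controls (pre against post, transition phase excluded) as the estimand for the 20% hypothesis, with level and trend as supporting results. It matches that hypothesis but gives up the adjustment for differing pre-trends that motivates the design, so this is a choice to argue openly.

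Items 1 and 2 cost a rewritten paragraph, a short simulation and less favorable figures. They change no data and no planned test, and can be done before the data extraction planned for September 2027.

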### Ethical Considerations

Evaluation of the *CQFD-I* program was approved by the research ethics board of the Centre intégré de santé et de services sociaux de l'Outaouais in May 2021 (2020-305_171) and by the Comité d’éthique de Brest in March 2023 (B2023CE.18). No consent to participate is required as we will exclusively interact with nonidentifying data in the context of official procedures overseen by governmental bodies in both implementation jurisdictions. We will only extract and report data aggregated at the population level. This outcome evaluation will thus constitute a minimal-risk project for all individuals involved, with no risk to the privacy or confidentiality of any participant. Additional precautions will be undertaken as required by the public agencies providing access to data in Quebec and France.

## Results

The CQFD-I program was conceptualized and refined from 2014 to 2020 through a series of meetings and negotiations between the 2 international partners, culminating in a version suited for implementation in Quebec and France despite differences in their medical and psychosocial service structures. The CQFD-I program’s timeline includes 3 phases: preimplementation (2015 to 2020), implementation (2020 to 2022), and postimplementation (2022 to 2024) phases. The implementation phase commenced on September 1, 2020, marked by the initial official meetings held within that month to brief stakeholders on the program’s strategies. Considering that (1) Brest Métropole was constituted in January 2015 [39] and (2) a law initiating a major health and social services reform was passed in Quebec in February 2015 [51], we define September 1, 2015, as the beginning of the preimplementation phase of the study. This 5-year period for data collection was established to ensure a sufficiently long baseline to reflect changes in policy. All 5 strategies of the CQFD-I program were fully implemented by September 1, 2022, marking the beginning of the postimplementation phase. For evaluation purposes, August 31, 2024, will be the last day of the postimplementation phase.

This project is funded by the Ministère de la Santé et des Services Sociaux du Québec, with access to data and expertise representing in-kind contributions from Santé publique France and INSPQ. Under the responsibility of the first author, data will be collected from public health databases in September 2027 to account for the delays necessary to confirm suicide deaths in official registers. Data analysis will be performed from September 2027 to June 2028.

## Discussion

### Anticipated Findings

In this paper, we present the study protocol for the outcome evaluation of the CQFD-I program, a multimodal suicide prevention program currently implemented in 2 sites, that is, Brest Métropole in Brittany, France, and the Outaouais region in Quebec, Canada. We hypothesize that after 2 years of the CQFD-I program’s implementation, there will be a 20% reduction in suicide mortality, hospitalizations due to suicide attempts, and ER visits for suicide attempts compared to control sites. Through this study, we will generate data for the first time on the effects of implementing a multimodal suicide prevention program at the population level in 2 countries not exclusively located in Europe. In addition to its general contribution to currently limited knowledge about the effects of multimodal suicide prevention programs, this study represents a proof of concept of sharing international resources to design a program targeting populations speaking a common language but residing in very different jurisdictions. Accordingly, positive results from this study would have profound implications on the potential to leverage international partnerships to disseminate best practices in suicide prevention, a promising avenue for low-income countries and underserved linguistic minority groups.

One limitation of this protocol is the reliance on administrative databases to ascertain suicide-related outcomes. While this allows for long-term follow-up across implementation phases and ensures comparable data quality between implementation and control sites, it may limit the interpretability of results. For instance, Quebec includes *ICD-10* code Y87.0 (sequelae of intentional self-harm, assault, and events of undetermined intent) for suicide attempts, whereas French databases do not. Even within jurisdictions, definitions differ: in Quebec, suicide attempt hospitalizations are coded with *ICD-10*, while ER visits rely on triage-based clinical judgment. To address these discrepancies, we will avoid assuming data source equivalence. First, suicide attempt rates will only be compared within the same jurisdiction. Second, each outcome—suicide mortality, hospitalizations, and ER visits—will be analyzed separately rather than combined for statistical power. While we expect all outcomes to decrease if the CQFD-I program is effective, reductions in only some outcomes would still be valuable results and warrant further research.

### Conclusions

Results may guide future research by offering valuable insights into directing suicide prevention efforts for geographically defined populations. The CQFD-I program created opportunities for participants from 2 distinct jurisdictions to reflect on the unique aspects of the health and social services systems and challenge assumptions that might otherwise limit their ability to innovate in suicide prevention. Program development and implementation benefited from sharing expertise and resources; however, they also highlighted new challenges for researchers to address regarding the operationalization and integration of suicide prevention strategies at the subnational level. Each of the CQFD-I program’s components had to be designed and operationalized to accommodate implementation in 2 distinct jurisdictions, a task that involved both anticipated and unforeseen challenges. The web portal required tailored promotional strategies aligned with local information consumption habits, demanding creativity from program implementers. Dissemination of the depression training program had to meet the high continuing education standards of primary care physicians, while suicide assessment and management training needed to be adapted to the staff training approaches of existing organizations. Standardizing postcrisis outreach and outpatient monitoring required a thorough understanding of clinical and managerial practices across multiple disciplines and institutions. The program’s implementation will be the topic of an upcoming paper that will go hand in hand with the results of the study described in this protocol.

## Abbreviations

CQFD-I: Coopération Québec-France contre la Dépression et l’isolement
ER: emergency room
ICD-10: International Classification of Diseases, 10th Revision
INSPQ: Institut national de santé publique du Québec
OSPI-Europe: Optimizing suicide prevention programs and their implementation in Europe
TREND: Transparent Reporting of Evaluations with Nonrandomized Designs
